### Exclusion criteria

Patients will be excluded if they meet any of the following criteria: (1) age below 18 or above 80 years; (2) pregnancy or lactation; (3) New York Heart Association Class IV chronic heart failure [26], or myocardial infarction within the previous 3 months; (4) uncontrolled blood loss; (5) cardiogenic shock; (6) advanced pulmonary fibrosis; (7) respiratory failure requiring non-invasive mechanical ventilation before enrollment; (8) severe, preexisting, parenchymal liver disease with clinically significant portal hypertension, Child-Pugh C stage cirrhosis [27], or acute liver failure [28]; (9) recipient of solid-organ or bone marrow transplant; (10) cardiopulmonary resuscitation within 72 h before enrollment; (11) invasive fungal infection [29, 30]; (12) active pulmonary tuberculosis [31]; (13) full-thickness thermal or chemical burn involving 30% or more of the body surface area; (14) evidence of clinically significant immunosuppression; (15) previous treatment with immunomodulatory agents, such as *Xuebijing*, thymosin, or intravenously administered immunoglobulin (IVIG) within 2 months before enrollment; (16) participation in an investigational clinical trial within 6 months before screening; (17) expected survival of less than 2 months or chronic vegetative state; (18) lack of commitment to full, aggressive life support; (19) history of hypersensitivity to ulinastatin. Clinically significant immunosuppression includes, but is not limited to, moderate or severe neutropenia (i.e., absolute neutrophil count < 1.0 × 10^9^/L), high-dose corticosteroids (corticosteroid equivalent of ≥ 20 mg prednisone every day for at least 2 weeks) prior to enrollment, immunomodulatory medications (e.g., cyclosporine, azathioprine, or OKT3), chemotherapy, or radiotherapy within 2 months before enrollment, known HIV seropositivity, non-remission stage of hematological/lymphoid malignancy, and any disease sufficiently advanced to suppress resistance to infection.

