### Interventions

The study group and the control group will receive ulinastatin (400,000 IU every 8 h) and placebo, respectively, for 10 days, with the first dose administered within 8 h of study enrollment. In particular, the study drug is reconstituted with 10 ml of normal saline, which will be further diluted in 100 ml of normal saline. The study drug is administered over 1 to 2 h with the use of specially designed administration sets to ensure blinding. Matching placebo vials, with identical reconstitution and infusion instructions to the ulinastatin vials, will be administered on the same schedule. Apart from ulinastatin treatment, all enrolled patients will receive standard care for sepsis and septic shock as per local protocols, including, but not limited to, antimicrobial agents, intravenously administered fluids, enterally or parenterally administered nutrition, transfusion of blood and blood products, and life-sustaining therapy (e.g., vasopressors, mechanical ventilation, and renal replacement therapy). The treating physicians are encouraged to adhere to the updated Surviving Sepsis Campaign guidelines [34], although the final decision is at the discretion of the treating physicians.

Doses of ulinastatin showed significant variation in different clinical trials, from 300,000 IU [35] to 1,200,000 IU [36] daily. In a surveillance study of 17 ICUs of China Critical Care Clinical Trials Group (CCCCTG), 15 reported the use of ulinastatin as adjunctive treatment of sepsis, with daily dose range 200,000 IU to 2,000,000 IU ([name], personal communication). The safety and tolerance of multi-dose (up to 1,200,000 IU qid) of ulinastatin have been evaluated in healthy volunteers without any serious adverse events (SAEs) [37]. In a rat model of sepsis, treatment with high-dose ulinastatin (200,000 IU/kg) significantly inhibited the production of TNF-α, P-selectin, and thrombin-antithrombin complex compared with a low dose (50,000 IU/kg) [38]. In a previous clinical study, a high dose of ulinastatin (300,000 IU twice a day) was associated with a significantly better clinical outcome and cytokine assays compared with middle- and low-dose ulinastatin (200,000 and 100,000 IU twice daily, respectively) [39]. The dose of ulinastatin in this trial was determined by consensus based on the above evidence.

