### Concomitant interventions

Participants may receive stress-dose corticosteroids in the form of hydrocortisone at a daily dose of ≤ 300 mg for the treatment of refractory septic shock. In addition, the use of non-steroidal anti-inflammatory drugs is also acceptable for the purpose of defervescence according to the local protocol. Other immunomodulatory agents (e.g., *Xuebijing*, thymosin, and polyclonal IVIG) should not be used during the study period, except for the purpose of treating underlying diseases (e.g., IVIG for Guillain-Barré syndrome). Use of all above drugs, if any, should be documented in the electronic Case Report Form (eCRF). No other agents with anti-inflammatory effects are allowed during the study period.

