### Secondary endpoints

The secondary endpoints of this trial include following:Mortality analysis: including 90-day all-cause mortality, ICU mortality, hospital mortality, length of stay in ICUOrgan failure and supportive intervention requirements: including SOFA scores at baseline and days 1–10, 14, and 28; use of life-sustaining therapy (i.e., vasopressor, mechanical ventilation, renal replacement therapy); lactate levels at baseline and days 1, 3, 6, and 10; fluid balance during the first 10 daysInflammatory biomarkers: including high-sensitivity C-reactive protein (hs-CRP), tumor necrosis factor (TNF)-α, IL-6, and IL-10 at baseline and days 1, 3, 6, and 10Functioning: activities of daily living (ADL) level at baseline and hospital discharge [40]

We planned to collect data of organ dysfunction at baseline and various time points during the study. All the six domains of the SOFA score, including respiratory, coagulation, hepatic, cardiovascular, renal, and central nervous system, will be documented. Vasopressors, mechanical ventilation, and renal replacement therapy use will also be documented during the study as an assessment of organ dysfunction. New-onset organ dysfunction is defined as any increase of any domain in SOFA score.

Serum levels of inflammatory biomarkers (hs-CRP) and cytokines (IL-6, IL-10, and TNF-α) will be measured with a chemiluminescence assay and turbidimetric inhibition immunoassay, respectively, in a central laboratory (Kingmed Center for Clinical Laboratory). All the assay chipsets were manufactured by Siemens Healthcare Diagnostics, UK.

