### Data management

Data management will be performed by trained staff at each participating center using the electronic data capture (EDC) system (https://edc702.drugchina.org). The quality of trial data management will be guaranteed by the reliability, access control, and traceability of the EDC system. Data collection will be restricted to those variables necessary to define baseline patient characteristics (demographics, sepsis diagnosis, concurrent medical conditions and comorbidities, inclusion and exclusion criteria, severity of illness and organ dysfunction scores, vital signs, and laboratory results), the delivery of the study drugs, potential confounding co-interventions (life-sustaining therapies, and use of other immunomodulatory agents), and outcomes (vital status at ICU and hospital discharge, day 28, and day 90, length of stay in ICU and hospital). Randomized participants will be followed up until either death or 90 days after randomization, whichever comes first. Follow-up will be attended by study staff by either direct contact with the patient or their next of kin. Participants who withdraw from the study for any reason will be followed up according to the study follow-up schedule and analyzed on the ITT principle.

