### Data analysis

All analyses will be performed according to the ITT principle. A *P* value < 0.05 is considered statistically significant. All tests are two-sided with no adjustment for multiple comparisons. Continuous variables are reported as means and standard deviations or medians and interquartile ranges. Categorical variables are reported as proportions. Pearson’s chi-squared test and adjusted multivariable analysis will be applied for the primary outcome. We plan to perform subgroup analyses for the primary outcome for predefined variables: presence or absence of septic shock, time from onset of sepsis to study enrollment (≤ 24 h or 24 to 48 h), and concomitant use of corticosteroids (yes or no). All the other data including age, APACHE II score, acute respiratory distress syndrome (ARDS) [46], systemic inflammatory response syndrome [47], acute circulatory failure [48], and number of failed organs will be presented as descriptive results. Pearson’s chi-squared test will be used for comparison of mortality outcomes between groups. The *t* test will be used for comparison of SOFA scores, life-sustaining interventions, lactic acid levels, fluid balance, inflammatory biomarkers, and function indicators between groups. A paired *t* test will be used for comparison of baseline and changes during the intervention.

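### The predefined corticosteroid subgroup is not limited to use at randomisation, so its treatment effects on 28-day mortality can be biased; the primary comparison is unaffected

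*Protocol article*

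**What the plan says.** The Data analysis section states: "We plan to perform subgroup analyses for the primary outcome for predefined variables". It names three: septic shock (present or absent), time from onset of sepsis to enrolment, and "concomitant use of corticosteroids (yes or no".

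The first two are fixed at entry. Septic shock is also a stratification factor under Randomization. The third has no time window.

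The word concomitant is also the title of the Concomitant interventions section, which covers drugs allowed while the study runs. It says: "Participants may receive stress-dose corticosteroids in the form of hydrocortisone", up to a stated daily dose, "for the treatment of refractory septic shock". Use is to be documented in the eCRF. Under Interventions, clinicians are encouraged to follow guidelines for standard care, but "the final decision is at the discretion of the treating physicians".

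The Data management section lists baseline characteristics separately from "potential confounding co-interventions (life-sustaining therapies, and use of other immunomodulatory agents". Steroids are not named there, but they plausibly belong with those co-interventions.

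**The concern.** Randomisation makes the arms comparable within any group defined by information available before treatment. It gives no such guarantee for a group defined by something that happens afterwards and that treatment may alter.

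The trigger for hydrocortisone is refractory shock. The trial tests whether ulinastatin changes closely related states: SOFA scores and "use of life-sustaining therapy (i.e., vasopressor, mechanical ventilation, renal replacement therapy" are secondary endpoints. If the drug keeps some patients out of refractory shock, the steroid-treated patients on ulinastatin are a differently selected group from those on placebo. The untreated patients are then differently selected too. In addition, a patient who dies early cannot go on to start steroids, so membership depends partly on the outcome being compared.

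A real benefit could look small in both strata, or harm could appear where there is none. The section tests at P < 0.05 without multiplicity adjustment and does not label the subgroups exploratory, so such a result could be read at face value.

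**Working it through.** **1. What the plan supplies.** It gives no steroid-use rate, no subgroup mortality and no effect of ulinastatin on steroid use, so there is no subgroup figure to reproduce. The only relevant number is the assumed control mortality of 33.5% (Sample size estimation). Everything below is illustrative.

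**2. Is the variable a baseline one?**
- Septic shock: known at randomisation, because it is a stratification factor.
- Time from onset to enrolment: known at enrolment.
- Corticosteroids: may begin at any time during the study, and no passage restricts the subgroup to earlier use.

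**3. Severity model, real benefit.** Assume post-randomisation severity S = Z − 0.4A + 0.6E, with Z and E standard normal and A = 1 for ulinastatin. The SD of S is √1.36 = 1.17, so the shift is 0.4/1.17 = 0.34 SD. Death follows logit P = −1 + 1.2S. The figures come from numerical integration.

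(a) Steroids given whenever S > 0.6. Use is 1 − Φ(0.6/1.17) = 30.4% on placebo and 1 − Φ(1.0/1.17) = 19.6% on ulinastatin.

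| | Placebo | Ulinastatin | Difference | Share of 7.4 lost |
|---|---|---|---|---|
| All | 32.4% | 25.1% | −7.4 | – |
| Steroid yes | 63.0% | 60.8% | −2.2 | 70% |
| Steroid no | 19.1% | 16.4% | −2.7 | 63% |

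(b) Same model, but the decision is noisy: steroids given if S plus an independent standard normal exceeds 0.8. Use is 30.1% vs 21.7%.

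| | Placebo | Ulinastatin | Difference | Share of 7.4 lost |
|---|---|---|---|---|
| Steroid yes | 54.4% | 49.0% | −5.5 | 26% |
| Steroid no | 22.9% | 18.4% | −4.5 | 39% |

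**4. Severity model, no effect on death.** Keep rule (a), but let death depend only on baseline severity: logit P = −1 + 1.2Z. Overall mortality is 31.4% in both arms.
- Steroid yes: 53.8% vs 59.7%, a false harm of 5.9 points.
- Steroid no: 21.6% vs 24.5%, a false harm of 2.9 points.

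**5. A simpler model, also with no effect on death.** Take three equal strata with mortality 10%, 30.5% and 60%; the mean is (10 + 30.5 + 60)/3 = 33.5%, the plan's control rate. Assume steroid use of 5%, 25% and 60% on placebo, with the drug halving only the middle figure to 12.5%.
- Steroid yes, placebo: (0.05×10 + 0.25×30.5 + 0.60×60)/0.90 = 44.125/0.90 = 49.0%.
- Steroid yes, ulinastatin: (0.05×10 + 0.125×30.5 + 0.60×60)/0.775 = 40.3125/0.775 = 52.0%, so +3.0 points.
- Steroid no: 56.375/2.10 = 26.8% vs 60.1875/2.225 = 27.1%, so +0.2 points.

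Larger assumed shifts in use give +5.2 points in steroid yes (10/40/70% vs 5/20/70%) and +8.8 points (5/40/70% vs 1/8/70%). Steroid no moves by less than 1 point in each.

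**6. The zero case.** If steroid use is the same in both arms within each severity level and death is unaffected, both differences are exactly 0.

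None of these models includes the need to survive until steroids are given. That mechanism is argued, not sized.

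**The case against.** Five points can be made against this.

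- **The primary result is safe.** It is the overall intention-to-treat comparison. Sample size, randomisation and secondary endpoints do not depend on this subgroup. This stands and limits the severity.
- **The bias is conditional.** It needs ulinastatin to alter steroid use, or early death to differ by arm. A reader might infer that the subgroup effects are certainly biased, but the document gives no data on either condition. This stands: the effects can be biased.
- **Some use may precede randomisation.** Enrolment may come up to 48 h after the Sepsis-3 criteria are met, and patients may enter in vasopressor-dependent shock. The steroid exclusion covers only "corticosteroid equivalent of ≥ 20 mg prednisone every day for at least 2 weeks", so short-course use at entry is possible. A reader might infer that the variable is wholly post-randomisation. The text supports only that its timing is open and includes later use.
- **A two-thirds loss is near a worst case.** It needs a deterministic steroid rule on the same severity measure that alone drives death. Decisions left to physicians will be noisier, and case (b) loses much less. This stands, so two thirds is one end of a range and not an expected size.
- **The analysis plan may define the timing.** It may, and it is not shown. But the article does not leave the matter open: it names a variable and calls it predefined. A baseline-only definition would narrow the published one. This objection does not remove the point.

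**Conclusion.** The point holds in conditional form. The protocol predefines a mortality subgroup on corticosteroid use that, as written, includes use started after randomisation for a state that ulinastatin may influence. Effects within that subgroup can therefore be biased.

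The possible size depends entirely on assumptions. It ranges from none, through a loss of about 25–40% to about two thirds of a true benefit of some 7 points. Where the drug has no effect on death, the severity model gives about 3 to 6 points of false harm. The three-stratum model gives 0 to about 9 points in steroid users and under 1 point in non-users. The true direction cannot be determined from the document.

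It would be wrong to infer that the trial's main conclusion is compromised, because the primary analysis does not use this variable. The definition should be fixed, but this is not a defect that invalidates the trial.

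**What to change.** In the Data analysis section, define the subgroup as corticosteroid use at or before randomisation (yes or no), taken from the start dates in the eCRF. Report corticosteroid use after randomisation by arm as a description only, not as a subgroup for treatment effect.

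The cost is about one line of wording, with no extra patients and no change to care. The article says use is recorded but does not say that start dates are, so confirm that they are captured. The article describes the trial as still recruiting, so the definition can be settled before unblinding. The real downside is precision: the yes stratum at baseline will be smaller than the stratum of patients who ever used steroids, and its estimate will be less precise.

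### Plain t tests are fixed for late SOFA, discharge ADL and use of organ support with no rule for patients who die; this tends to bias SOFA and ADL against a drug that lowers mortality

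*Protocol article*

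**What the plan says.** The Secondary endpoints section of the protocol article lists "SOFA scores at baseline and days 1–10, 14, and 28", "lactate levels at baseline and days 1, 3, 6, and 10", "activities of daily living (ADL) level at baseline and hospital discharge", and "use of life-sustaining therapy (i.e., vasopressor, mechanical ventilation, renal replacement therapy"). It does not say whether organ support is scored as yes/no, as days of use or as support-free days.

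The Data analysis section names one between-group method for all of these: a t "test will be used for comparison of SOFA scores, life-sustaining interventions, lactic acid levels, fluid balance, inflammatory biomarkers, and function indicators between groups". For change from baseline it adds that a paired t "test will be used for comparison of baseline and changes during the intervention". Its general rule is "All analyses will be performed according to the ITT principle".

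Under Data management, "Randomized participants will be followed up until either death or 90 days after randomization, whichever comes first". No section says how a patient who has died enters the SOFA, ADL or organ-support comparisons.

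**The concern.** A t test needs one number per patient. A patient who dies has no later SOFA, and one who dies in hospital has no discharge ADL. The intention-to-treat sentence assigns patients to arms but cannot supply a value that does not exist. Without a death rule, the natural result is a comparison of those who still have a value, and the paired test has the same gap because it needs both measurements.

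If the drug lowers mortality as planned, its survivors include patients who would have died on placebo. Those patients are probably sicker than the other survivors, so the ulinastatin survivor mean is pulled towards worse scores. The trial could then report a mortality benefit beside organ-function results that look neutral or unfavourable only because of who survived. The Discussion says that the trial wants more organ-function measures because of the Sepsis-3 definition, so readers will look at these results. The Background section also faults an earlier Indian trial for withdrawing patients after randomization because of early death. A survivor-only t test leaves out early deaths in a similar way.

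Organ support raises a separate point. Use of a therapy reads as yes/no, and the same section reports categorical variables as proportions, yet it assigns a t test.

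**Working it through.** **Inputs from the article.** Control 28-day mortality 33.5%; absolute reduction 14.5 points, so 19.0% on ulinastatin; N = 348; power 80%; loss 20% (Sample size estimation). Allocation 1:1, so 174 per arm (Randomization). Two-sided 0.05 (Data analysis).

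**The plan's own figure.** With unpooled variance, n per arm = (1.960 + 0.842)² × (0.335 × 0.665 + 0.19 × 0.81) / 0.145² = 140.6. Dividing by 0.80 and doubling gives about 352. With pooled variance, n = 144 per arm; multiplying by 1.2 gives 173 per arm, 346 in total. The stated 348 lies between the two, so the mortality rates used below are those behind the sample size.

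**Patients without a day-28 SOFA because of death.**
- Control: 174 × 0.335 = 58.3, leaving about 116.
- Ulinastatin: 174 × 0.19 = 33.1, leaving about 141.

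**Shift in the survivor mean.** Assume that the drug changes survival only, and that nobody who would survive on placebo dies on ulinastatin. Per 100 patients, 66.5 survive on either arm (mean m) and 14.5 survive only on ulinastatin (mean m + D).
- Control survivor mean: m.
- Ulinastatin survivor mean: (66.5 m + 14.5 (m + D)) / 81 = m + 0.179 D.

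| D (assumed) | Shift against ulinastatin, SOFA points |
|---|---|
| 2 | 0.36 |
| 4 | 0.72 |
| 6 | 1.07 |

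**Simulation of the t test on survivors** (174 per arm, 4,000 repeats). Assumed: SOFA SD 4 and log-odds of death rising by 1.2 per SD of severity. The correlation of SOFA with severity was varied. In the first three result columns the drug affects mortality only.

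| Correlation | Mean shift | Ulinastatin looks worse | Significantly worse (nominal 2.5%) | Mean difference with a true 0.5-point benefit | Looks worse despite that benefit |
|---|---|---|---|---|---|
| 0 | 0.00 | 50% | 3% | −0.51 | 15% |
| 0.3 | +0.16 | 63% | 5% | −0.35 | 24% |
| 0.5 | +0.27 | 69% | 7% | −0.24 | 31% |
| 0.7 | +0.36 | 77% | 11% | −0.14 | 39% |

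With a true 1.0-point benefit, the drug looks worse in 5%, 6% and 10% of trials at correlations 0.3, 0.5 and 0.7.

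**Days of organ support, if that is what is meant.** Assume 5 days in patients who survive on either arm. Control mean = 0.665 × 5 + 0.335 × (days in those who die). Ulinastatin mean = 0.665 × 5 + 0.145 × (days in those saved) + 0.19 × (days in those who die).
- Those who die 3 days, those saved 8 days: 4.33 (control) versus 5.06 (ulinastatin).
- Those who die 8 days, those saved 5 days: 6.01 versus 5.57, the opposite direction.

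**The case against.** The strongest reply is that the article never says that only patients with a value are compared. Scoring of deaths is commonly left to a statistical analysis plan, and none is shown here. This stands in part: the survivor-only comparison is an inference, and an unseen plan could assign scores to deaths. But the article does fix the test. A plain t test does not suit discharge ADL or late SOFA at this level of mortality, nor a yes/no variable.

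A reader might go further and infer that a life-saving drug will look worse on these outcomes. The document does not support that. The direction is a tendency: with no link between SOFA and severity there is no shift, and with a true 0.5-point benefit the simulated mean difference still favours the drug. A reader might also take a shift of about one SOFA point as the expected size. That needs a 6-point gap, for which the article gives no basis, and a 2-point gap gives 0.36. Nor does it follow that early death must look like less organ support. The article defines no days-of-support measure, and the direction reverses under plausible inputs. Lactate, biomarkers and fluid balance stop at day 10, when fewer deaths have occurred, so they are less exposed.

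It is also fair to object that ranking death as worst makes SOFA and ADL partly restate mortality. In a simulation at the planned death rates, with identical SOFA in survivors (mean 4, SD 4, assumed), the rank test favoured ulinastatin significantly in about 67% of trials. That is a real cost of the remedy.

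**Conclusion.** The point holds as a should-fix for secondary endpoints. Followed as written, the t tests for late SOFA and discharge ADL compare groups that randomization no longer balances, at day 28 about 116 against 141 survivors. They tend to be biased against a drug that lowers mortality.

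The size is about 0.18 × D SOFA points. It rests on the planned death rates, on no patient being harmed by the drug, and on an assumed D. The simulated shifts of 0.16 to 0.36 points lie at the low end of that range. A true benefit may be attenuated rather than reversed, and bias in any days-of-support measure can go either way. For yes/no organ support the problem is simply the type of test.

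The primary endpoint, 28-day all-cause mortality by chi-squared test, is not affected.

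**What to change.** - **Late SOFA (days 14 and 28) and discharge ADL:** use a comparison that includes deaths. Give death the worst rank and use a rank test or a proportional-odds model adjusted for septic shock, which is already a stratification factor. Label survivor-only means as descriptive.
- **Organ support:** say which measure is meant. For yes/no use, apply the chi-squared or a stratified test. For an amount, use vasopressor-, ventilator- and renal-replacement-free days with death scored 0, over the period for which daily support data are collected. The article says only that use is documented during the study, so check that period first.

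**Cost.** The change is to the analysis wording plus a few derived variables. Vital status and SOFA are already collected, the article reports the trial as still recruiting, and no interim analysis is planned, so the change can be made before unblinding. The composite ranks partly reflect mortality and are harder to read than means, so they should be reported beside the mortality result and not presented as separate evidence on organ function.

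### The paired t test from baseline does not compare the arms, and the unadjusted between-group t test leaves measured baseline values unused for SOFA, lactate and biomarkers

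*Protocol article*

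**What the plan says.** The Data analysis section of the protocol article names the tests for the continuous secondary endpoints.

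- Between arms: the t "test will be used for comparison of SOFA scores, life-sustaining interventions, lactic acid levels, fluid balance, inflammatory biomarkers, and function indicators between groups". No covariate, transformation or time point is given.
- From baseline: a paired t "test will be used for comparison of baseline and changes during the intervention".
- Adjustment is named for mortality only: Pearson's "chi-squared test and adjusted multivariable analysis will be applied for the primary outcome".
- Skewness is allowed for in description: "Continuous variables are reported as means and standard deviations or medians and interquartile ranges". No matching choice is made for the tests.

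The Secondary endpoints section schedules a baseline value for each of these measures: "SOFA scores at baseline and days 1–10, 14, and 28", "lactate levels at baseline and days 1, 3, 6, and 10", and hs-CRP, TNF-α, IL-6 and IL-10 on the same days as lactate. The Discussion says that the biomarkers are meant to inform on how ulinastatin works.

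**The concern.** Two separate things are at issue.

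First, a paired test asks whether values moved between baseline and a later day. Both arms receive standard sepsis care (Interventions section), so values can move in both arms whether or not the drug does anything. The trial is a placebo-controlled superiority trial, and its mechanism question is about the difference between arms. A test of change over time cannot answer that, whether it is run within each arm or on all patients together.

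Second, the test that does compare arms is stated without the baseline value. That value is measured before treatment and probably predicts the later one. Leaving it out makes the comparison less precise than the data allow. If cytokines and CRP are right-skewed, a t test on untransformed values loses more. At stake are precision and interpretation for the organ-function and mechanism endpoints, not the primary result.

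**Working it through.** **1. The plan's own figure.** The article gives no power figure for the continuous secondary endpoints. Its only one is the primary-endpoint size of 348 (33.5% vs 33.5 − 14.5 = 19.0%, two-sided 0.05, 80% power, 20% loss).

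- Pooled-variance formula: 144 per arm, 288 in total; 288 × 1.2 = 345.6, so 346; 288 / 0.8 = 360.
- Unpooled: 141 per arm, or 354 after dividing by 0.8.
- Working back: 348 × 0.8 / 2 = 139 per arm, with 78.8% power.

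So 348 is reproduced closely enough. It is used below only to supply 139 evaluable patients per arm.

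**2. The paired test.** Simulation of 4,000 trials per row, 139 per arm, baseline/follow-up correlation ρ = 0.5 (assumed).

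| Fall shared by both arms | Extra fall on drug | Both paired tests significant | Exactly one significant |
|---|---|---|---|
| 0.17 SD | none | 27% | 50% |
| 0.24 SD | none | 63% | 33% |
| 0.50 SD | none | 100% | 0% |
| 0.50 SD | 0.336 SD | 100% | 0% |

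The last two rows are the point: the paired results are the same with and without a drug effect. The first two rows show that comparing the arms' paired P values can also suggest a difference where none exists. With paired power p in each arm, the chance of exactly one significant result is 2p(1 − p). This cannot exceed 50% and falls to nothing when the common change is large.

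**3. Is the between-group t test valid?** In the same simulations with no drug effect it rejected in 4.6–5.1% of trials on the log scale and 4.1–4.6% on the raw scale. With a true log-scale difference of −0.336, the mean log-scale estimate was −0.338. With complete data it is valid, and the mean difference is unbiased.

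**4. What the unused baseline costs.** Set the variance of the follow-up-only contrast to 1. A comparison of change scores has 2(1 − ρ), and a baseline-adjusted comparison (ANCOVA) has 1 − ρ². The effect that the unadjusted t test detects with 80% power is (1.960 + 0.842) × √(2/139) = 0.336 SD. Adjusted power is Φ(2.802 / √(1 − ρ²) − 1.960).

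| ρ (assumed) | Change score | ANCOVA | Power for 0.336 SD | Effect detectable at 80% | Equivalent total N for 278 |
|---|---|---|---|---|---|
| 0.3 | 1.40 | 0.91 | 83.6% | 0.321 SD | 278 / 0.91 = 305 |
| 0.5 | 1.00 | 0.75 | 89.9% | 0.291 SD | 278 / 0.75 = 371 |
| 0.7 | 0.60 | 0.51 | 97.5% | 0.240 SD | 278 / 0.51 = 545 |

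The variance ratios do not depend on arm size. Nor do the powers, because the effect is set as the one that the unadjusted test finds with 80% power. Comparing change scores between arms is no substitute: it is worse than using no baseline when ρ is below 0.5, and worse than ANCOVA in every row.

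**5. Skewed markers.** Log-normal values, 139 per arm, ρ = 0.5, drug effect 0.336 SD on the log scale. This is a geometric mean ratio of exp(−0.336) = 0.71 at log-SD 1.0, and exp(−0.504) = 0.60 at log-SD 1.5.

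| Log-SD (assumed) | Raw t test | Log t test | Log ANCOVA |
|---|---|---|---|
| 1.0 | 58.9% | 79.3% | 89.8% |
| 1.5 | 40.6% | 80.5% | 89.6% |

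**The case against.** The strongest reply is that the article does plan a direct between-group test for these same outcomes, and nowhere proposes to compare paired results across arms or to treat them as evidence of efficacy. That is right. The paired test is a fault only in that its role is not stated.

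It can also be said that transformation, time points and longitudinal models belong in an analysis plan that is not shown, and that the Randomization section already foresees hospital as a covariate. That stands too: their absence from an article is not a finding. What remains is that the article does name a method for these endpoints, and an analysis that follows it as written would leave out the baseline.

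Stronger readings are tempting, but the documents do not support them.

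- *The t tests do not estimate the drug's effect.* The between-group test does, as step 3 shows.
- *Each day is tested separately, on the raw scale, with paired tests within each arm.* None of these is written; each is an inference from a condensed text.
- *Half of trials would show a false arm difference.* This is the maximum of 2p(1 − p). It needs a modest common change and a reading that the article does not propose.
- *Many tests at 0.05 will yield chance positives.* The article says openly that "All tests are two-sided with no adjustment for multiple comparisons". For secondary endpoints that is a disclosed choice, and it is not part of this point.

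**Conclusion.** The point holds as a minor, nearly free improvement on secondary endpoints. The paired t test carries no information on ulinastatin versus placebo and should be descriptive only; this follows from its construction and needs no assumption.

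The between-group t test is valid with complete data but inefficient. The gain from adjustment ranges from small (variance 0.91, power 80% to about 84%) at ρ = 0.3 to large (0.51, about 97.5%) at ρ = 0.7. The further loss from skewness is conditional on an untransformed test and on log-SDs of 1.0 to 1.5. The documents give neither correlations nor spreads, so these are ranges, not estimates for this trial.

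Values missing after death are a separate matter: the planning assumption is 33.5% vs 19.0% mortality by day 28. Baseline adjustment alone does not resolve it. The primary mortality analysis and N = 348 are unaffected.

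**What to change.** In the Data analysis section, or in the analysis plan if it does not already do so:

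- State that drug effect on SOFA, lactate and the biomarkers is judged only by a between-arm comparison adjusted for the baseline value, by ANCOVA or a repeated-measures model, with septic shock and centre (the randomisation factors) as covariates.
- Analyse skewed markers on the log scale and report the ratio of geometric means with its 95% confidence interval.
- Keep changes from baseline as description by arm, without using their P values as evidence of effect.

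The cost is analysis wording, and results given as ratios rather than mean differences for the log-scale markers. No visit, sample or patient is added.
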